#### Randomization, treatment assignment and allocation concealment

Randomization will be undertaken during normal working hours (Monday to Friday from 9:00 to 17:00) by the German Rheumatologic Research Center (Deutsches Rheumatologisches Forschungszentrum, DRFZ) of participating centers upon receipt of a randomization request form and after blinded review of X-rays of both hands.

Identical HCQ and placebo capsules will be produced to ensure allocation concealment. Upon production, study medication will be packed into numbered bottles according to a randomization schedule. This will be prepared by the DRFZ using a computerized random number generator, thereby guaranteeing full allocation concealment. Trial medication will be issued in numerical order by the pharmacy of the Charité - Universitätsmedizin Berlin. Participants in each site will be randomly assigned to the intervention arm or the placebo arm in a ratio of 1:1 and the randomization will be double-blind.

#### Blinding

As this is a double-blind study, all parties involved including the investigator, study coordinator, and subject will remain blinded to each subject’s treatment throughout the course of the study. The blind will be maintained at all times until all data has been collected and the study database locked. Participants will be randomized centrally by computer generated random numbers stratified by center. Patients and investigators are blind to the treatment allocation. A sealed envelope containing the blinded information will be provided to the investigator and retained by him/her in a locked or secured area. This envelope may be opened in the case of emergency. Unopened envelopes will be returned to the sponsor at the end of the study. Use of NSAIDs and rescue medication (acetaminophen) will be assessed carefully throughout the trial. The possible influence of these drugs on the outcome will be discussed. Radiographs will be read in a concealed time order by two readers blinded to treatment assignment.

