#### Statistical methods

All patients who received at least one dose of the study medication will be included in the statistical analysis of the efficacy and safety of HCQ (modified intention-to-treat (mITT) population). To control the familywise error rate of 5%, a closed test procedure was applied [30]. In the first step, the first primary hypothesis is tested by means of the multiple endpoint tests according to Läuter and O’Brian [31]. Using this test the outcome in the AUSCAN scales pain and hand function at week 52 is compared between the treatment groups. The multiple endpoint test compares a standardized sum of both outcome measures (AUSCAN pain and function). Since we can assume that the outcome in pain and hand function are correlated, this test is more powerful than a Bonferroni-type test procedure or Hottelling’s T^2^ test [30, 32]. In the case of a significant difference of the first primary hypothesis, the second primary hypothesis (radiographic outcome at week 52) will be tested by means of an analysis of covariance (ANCOVA) based on ranks (nonparametric ANCOVA). Parametric ANCOVA with baseline status as co-variable will be applied to compare secondary outcomes (pain, function, quality of life parameters (SF-36)). Changes in the co-use of NSAIDs and/or analgesics will be compared between both groups. To estimate whether any imbalance in the use might have influenced the outcome in pain and function the suggestions by Dougados *et al*. for comparing different drugs and different dosages will be considered [33]. In the unlikely case that in the verum arm the dosages are more frequently increased by 50% or more (including an increase from 0 mg to half of the full dosage), this finding will be taken into account in the interpretation of the results.

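### Randomization is stratified by center, but none of the analyses described in the article includes center, so the tests are slightly conservative if center is prognostic

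*Protocol article*

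**What the plan says.** On allocation, the Blinding section says: "Participants will be randomized centrally by computer generated random numbers stratified by center". The section on randomization, treatment assignment and allocation concealment agrees: "Participants in each site will be randomly assigned to the intervention arm or the placebo arm in a ratio of 1:1". Center is the only stratification factor named.

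On analysis, the Statistical methods section gives three procedures under a 5% familywise error rate:

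- **First primary hypothesis:** a multiple endpoint test comparing a standardized sum of AUSCAN pain and function between the two arms. No covariate or stratum is named.
- **Second primary hypothesis (radiographic outcome at week 52):** an ANCOVA on ranks. No covariates are listed.
- **Secondary outcomes:** "Parametric ANCOVA with baseline status as co-variable will be applied". Baseline is the only covariate named.

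The Sample size section plans 255 per group, for 95% power on the multiple endpoint test and 80% power on radiographic progression at an effect size of 0.25. The same effect size is used for AUSCAN function, for which at least 80% power is also claimed.

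**The concern.** Stratifying by center with 1:1 allocation in each site makes the two arms nearly equal in their mix of centers, so differences between centers largely cancel out of the treatment comparison. A test that ignores center still counts those differences as residual variation. Its standard error is then larger than the true sampling error of the treatment difference, and the test rejects less often than its nominal level allows.

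What is at stake is efficiency, not validity. The design has paid for balance by center, and the analysis as described does not collect the precision that this balance makes available. It matters most for the comparisons planned at an effect size of 0.25, where power is closest to the 80% target.

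**Working it through.** **Inputs from the protocol article.** 255 per group; effect sizes 0.4 (pain), 0.25 (function) and 0.25 (radiographic); 5% familywise error rate; 1:1 allocation within site, stratified by center.

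**Assumptions (not in the document).** Two-sided testing at 5%; exact balance within center; ICC, meaning the share of outcome variance that lies between centers, of 0.01 to 0.10. Normal-theory formulas stand in for the rank ANCOVA.

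**Step 1: reproduce the plan's figures.**

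- Required n per group at effect size 0.25 and 80% power: 2 × (1.960 + 0.842)² / 0.25² = 251.2, so 252. The plan has 255.
- Power with 255 per group: the noncentrality is 0.25 × √(255/2) = 2.823, and Φ(2.823 − 1.960) = Φ(0.863) = 80.6% (80.4% with the noncentral t).
- Multiple endpoint test: the effect size of the standardized sum is (0.4 + 0.25)/√(2 + 2r), where r is the correlation between pain and function, not stated. The least favorable case, r = 1, gives 0.325 and 95.6% power. A smaller r gives more.

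The stated 80% and 95% both reproduce.

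**Step 2: effect of leaving center out.** With balance within center, the true standard error of the difference is √(1 − ICC) times the one the unadjusted test uses. Hence:

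- overstatement of the standard error: 1/√(1 − ICC) − 1
- actual type I error: 2 × [1 − Φ(1.960/√(1 − ICC))]
- power, unadjusted: Φ(0.863/√(1 − ICC))
- power with center in the model: Φ(2.823/√(1 − ICC) − 1.960)

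| ICC (assumed) | SE too wide by | Actual type I error | Power, unadjusted | Power, center in model | Difference (points) |
|---|---|---|---|---|---|
| 0 | 0% | 5.0% | 80.59% | 80.59% | 0 |
| 0.01 | 0.5% | 4.9% | 80.71% | 80.98% | 0.3 |
| 0.02 | 1.0% | 4.8% | 80.83% | 81.37% | 0.5 |
| 0.05 | 2.6% | 4.4% | 81.20% | 82.54% | 1.3 |
| 0.10 | 5.4% | 3.9% | 81.85% | 84.51% | 2.7 |

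Worked line, ICC 0.10: √0.90 = 0.9487. Type I error is 2 × [1 − Φ(2.066)] = 3.9%. Unadjusted power is Φ(0.863/0.9487) = Φ(0.910) = 81.85%. Adjusted power is Φ(2.823/0.9487 − 1.960) = Φ(1.016) = 84.51%.

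The right comparator for the adjusted power is the unadjusted power on the same row, not the 80.6% that applies with no center effect. Stratification alone already lifts the unadjusted figure a little.

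**Step 3: simulation with near rather than exact balance.** Assuming 30 centers of 17 patients (5,000 runs per setting), unadjusted type I error was about 4.6% at ICC 0.05 and 4.5% at ICC 0.10. Power was 81.2% unadjusted against 82.5% adjusted at ICC 0.05, and 81.6% against 84.2% at ICC 0.10. The direction and size agree with the formulas.

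**The case against.** **Silence is not exclusion.** The article condenses a fuller protocol. It calls the radiographic analysis an ANCOVA without naming any covariate, so its list is plainly abbreviated, and stratum terms are commonly fixed in the SAP. This stands as a limit: the article does not show that center will be left out, only that the analyses it describes do not contain it. It does not remove the point, because the article does name a covariate for the secondary analyses and names baseline alone.

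**The effect is small and on the safe side.** This also stands. Type I error is not inflated, the sample size does not change, and at 255 per arm unadjusted power is above 80% at every ICC in the table. The first primary test is planned at 95% power and has more room still. Radiographs are read by two blinded readers, which may keep between-center variance in that endpoint low.

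**Two stronger readings are not supported.**

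- A reader might infer that the supply arrangement defeats the stratification, since one pharmacy issues the bottles: "Trial medication will be issued in numerical order by the pharmacy of the Charité - Universitätsmedizin Berlin". But the article nowhere describes a single trial-wide sequence. It says that "study medication will be packed into numbered bottles according to a randomization schedule", and it states 1:1 assignment in each site. Numerical-order issue from a central pharmacy fits a schedule with number blocks per center, so there is no contradiction between the two sections.
- A reader might infer that omitting center puts the planned power at risk. At the planned numbers it does not. Power at effect size 0.25 could fall below 80% if enough patients lacked week-52 data, but the cause would then be the lost patients rather than the omission of center.

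**Conclusion.** The point holds as a modest, conditional one. The only stated stratification factor is absent from all three analyses that the article describes. If center is prognostic, those analyses are slightly conservative: over an assumed ICC of 0.01 to 0.10 with balance within center, standard errors are 0.5% to 5.4% too wide, type I error is 4.9% to 3.9%, and about 0.3 to 2.7 points of power are given up at effect size 0.25. The loss shrinks to nothing as the ICC approaches 0. The document gives neither the ICC nor the number of centers, so these figures are a range, not an estimate. The trial's validity and its stated power are not in question.

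**What to change.** Include center in the model for the multiple endpoint test, in the rank ANCOVA for radiographic progression and in the secondary ANCOVAs. Use a fixed effect with small centers pooled by a rule set before unblinding, or a random center effect. If the full protocol or SAP already does this, no change is needed. If center is left out deliberately, say so and give the reason.

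The cost is a few lines of analysis wording, with no new data, no extra patients and no change to the sample size.

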#### Statistical methods

All patients who received at least one dose of the study medication will be included in the statistical analysis of the efficacy and safety of HCQ (modified intention-to-treat (mITT) population). To control the familywise error rate of 5%, a closed test procedure was applied [30]. In the first step, the first primary hypothesis is tested by means of the multiple endpoint tests according to Läuter and O’Brian [31]. Using this test the outcome in the AUSCAN scales pain and hand function at week 52 is compared between the treatment groups. The multiple endpoint test compares a standardized sum of both outcome measures (AUSCAN pain and function). Since we can assume that the outcome in pain and hand function are correlated, this test is more powerful than a Bonferroni-type test procedure or Hottelling’s T^2^ test [30, 32]. In the case of a significant difference of the first primary hypothesis, the second primary hypothesis (radiographic outcome at week 52) will be tested by means of an analysis of covariance (ANCOVA) based on ranks (nonparametric ANCOVA). Parametric ANCOVA with baseline status as co-variable will be applied to compare secondary outcomes (pain, function, quality of life parameters (SF-36)). Changes in the co-use of NSAIDs and/or analgesics will be compared between both groups. To estimate whether any imbalance in the use might have influenced the outcome in pain and function the suggestions by Dougados *et al*. for comparing different drugs and different dosages will be considered [33]. In the unlikely case that in the verum arm the dosages are more frequently increased by 50% or more (including an increase from 0 mg to half of the full dosage), this finding will be taken into account in the interpretation of the results.

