**Methods/Design:**

OA TREAT is an investigator-initiated, multicenter, randomized, double-blind, placebo-controlled trial. A total of 510 subjects with inflammatory and erosive hand OA, according to the classification criteria of the American College of Rheumatology (ACR), with recent X-ray will be recruited across outpatient sites, hospitals and universities in Germany. Patients are randomized 1:1 to active treatment (HCQ 200 to 400 mg per day) or placebo for 52 weeks. Both groups receive standard therapy (non-steroidal anti-inflammatory drugs [NSAID], coxibs) for OA treatment, taken steadily two weeks before enrollment and continued further afterwards. If disease activity increases, the dose of NSAID/coxibs can be increased according to the drug recommendation. The co-primary clinical endpoints are the changes in Australian-Canadian OA Index (AUSCAN, German version) dimensions for pain and hand disability at week 52. The co-primary radiographic endpoint is the radiographic progression from baseline to week 52. A multiple endpoint test and analysis of covariance will be used to compare changes between groups. All analyses will be conducted on an intention-to-treat basis.

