The aim of OA TREAT is to investigate the efficacy of HCQ by clinical and radiological outcomes compared to placebo in patients with severe and refractory inflammatory hand OA. The co-primary hypotheses are that patients receiving HCQ have a lower Australian-Canadian OA Index (AUSCAN) score in the dimensions for pain and hand disability at week 52 and that they have a lower rate of radiographic progression from baseline to week 52 compared to patients receiving placebo.

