### Methodological aspects

#### Sample size

Our sample size considerations are based on the EULAR recommendations for the planning of RCTs in patients with hand OA [13]. We considered differences in change scores in the AUSCAN scales pain and hand function, which were observed in RCTs comparing NSAIDs (lumiracoxib or ibuprofen) with placebo as clinically relevant differences that also should be detected with a sufficient power in this RCT. For these reasons, we aim to detect an effect size (ES) of 0.4 for pain (SD: 4.3) and of 0.25 for function (SD: 7.3) [13, 29]. An ES of 0.25 is also considered to be relevant for changes in the radiographic scores. Based on these assumptions, a sample size of n=255 per group is sufficient to achieve a power of 95% for the multiple endpoint test (first primary hypothesis) and an 80% power for the second primary endpoint (radiographic progression). The sample size is also sufficient to achieve an at least 80% power when comparing the two AUSCAN subscales pain and hand function separately.

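### The gating AUSCAN sum test is described without a baseline covariate that the secondary analyses of the same scales already have, and its endpoint is worded both as change and as week-52 score

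*Protocol article*

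**What the plan says.** The confirmatory sequence is in Statistical methods. Step 1 is a multiple endpoint test of the Läuter and O'Brien type on a standardised sum of AUSCAN pain and function: "Using this test the outcome in the AUSCAN scales pain and hand function at week 52 is compared between the treatment groups". No baseline term is named. Only if this test is significant is radiographic outcome tested, by rank-based ANCOVA. For the same two scales as secondary outcomes, the section continues: "Parametric ANCOVA with baseline status as co-variable will be applied to compare secondary outcomes (pain, function, quality of life parameters (SF-36".

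The primary variable is worded in two ways.

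- **Change.** Abstract, Methods/Design: "The co-primary clinical endpoints are the changes in Australian-Canadian OA Index". The Discussion repeats this, and Sample size builds on it: "We considered differences in change scores in the AUSCAN scales pain and hand function". The abstract adds that the multiple endpoint test and analysis of covariance compare changes, without saying which method serves which endpoint.
- **Week-52 score or outcome.** The hypothesis closing the Background is that "patients receiving HCQ have a lower Australian-Canadian OA Index (AUSCAN) score in the dimensions for pain and hand disability at week 52". The endpoint list in Table 2 and the sentence in Statistical methods give the time point but do not mention change.

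**The concern.** Baseline AUSCAN is scheduled for every patient, and the plan uses it as a covariate when pain and function are analysed separately. The one AUSCAN analysis described without it is the confirmatory one, which also decides whether the radiographic hypothesis is tested at all. Precision that costs nothing appears to be left unused there.

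The wording adds a second difficulty. Without a baseline covariate, a test on change and a test on week-52 values have different variances and can give different p-values. With baseline in the model the two coincide. An unadjusted test therefore makes the endpoint wording matter, and the choice should not remain open once data are seen.

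**Working it through.** **Inputs from the protocol article.** Sample size: "we aim to detect an effect size (ES) of 0.4 for pain (SD: 4.3) and of 0.25 for function (SD: 7.3"); "a sample size of n=255 per group is sufficient to achieve a power of 95% for the multiple endpoint test"; 80% for an effect size of 0.25. Statistical methods: "To control the familywise error rate of 5%, a closed test procedure was applied". Discussion: power stays above 80% if both effects fall by 25%.

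**Assumptions, because no figure is given.** Two-sided 5% (this reproduces the stated powers); pain-function correlation ρ, taken as 0.7 unless varied; baseline to week-52 correlation r, taken as equal for both scales and varied; no dropout.

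**Step 1: reproduce the plan.** Power = Φ(d·√(n/2) − 1.96), with √(255/2) = 11.29.

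- One scale, d = 0.25: Φ(2.823 − 1.96) = 80.6%, as stated.
- Standardised sum: d = (0.40 + 0.25)/√(2 + 2ρ). At ρ = 1, d = 0.325 and power is 95.6%. At ρ = 0.7, d = 0.3525 and power is Φ(3.980 − 1.96) = 97.8%. At ρ = 0.5, power is 98.9%. The stated 95% holds for every ρ.
- Effects cut by 25%: 84.7% at ρ = 0.7, 80.6% at ρ = 0.9, 78.6% at ρ = 1. The claim of more than 80% holds up to about ρ = 0.9.

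**Step 2: what adjustment gains.** With baseline as covariate, residual variance is (1 + r)/2 of the change-score variance and 1 − r² of the week-52 variance.

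- Against change: 0.65 at r = 0.3, 0.75 at 0.5, 0.85 at 0.7, a cut of 35, 25 and 15%.
- Against week-52 values: 0.91, 0.75 and 0.51, a cut of 9, 25 and 49%.

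At r = 0.5 on change scores, d rises from 0.3525 to 0.3525/√0.75 = 0.407, and power from 97.8% to 99.6%. With effects cut by 25%, it rises from 84.7% to about 93%.

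**Step 3: what the wording could cost.** The planned effect sizes refer to change. The standard deviation of a week-52 value relative to that of change is 1/√(2(1 − r)), so d on raw week-52 values is multiplied by √(2(1 − r)). At r = 0.7 that is √0.6 = 0.775, and power is Φ(3.980 × 0.775 − 1.96) = 86.9%.

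Power of the sum test (ρ = 0.7, 255 per arm), at planned effects and, after the slash, at effects cut by 25%:

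| r | change, unadjusted | week-52, unadjusted | baseline-adjusted |
|---|---|---|---|
| 0.4 | 97.8 / 84.7% | 99.2 / 90.5% | 99.7 / 94.6% |
| 0.5 | 97.8 / 84.7% | 97.8 / 84.7% | 99.6 / 93.2% |
| 0.6 | 97.8 / 84.7% | 94.5 / 76.1% | 99.4 / 91.6% |
| 0.7 | 97.8 / 84.7% | 86.9 / 63.8% | 99.1 / 89.9% |

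A simulation of the three tests agrees: at r = 0.7 and planned effects it gave 97.9%, 87.2% and 99.2%.

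**The case against.** The strongest reply has four parts.

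1. **The gain at planned effects is small.** This stands: less than two percentage points at r = 0.5. A reader might infer a larger one from function alone, where an effect size of 0.25 with r = 0.5 goes from about 80% to 90%. That comparison does not describe the criticised test, and the plan already adjusts function for baseline when it is analysed separately.
2. **The two wordings may be one endpoint.** This stands in part. Statistical methods also speaks of the radiographic outcome at week 52, although that endpoint is defined elsewhere as progression from baseline. Its AUSCAN sentence may be similar shorthand for change. A lower week-52 score and a greater reduction also have the same expected treatment difference under randomisation. A reader might infer that raw week-52 values will be tested and the trial is therefore underpowered. The documents make the first possible but do not establish it, and the second also needs r of about 0.6 or more.
3. **Silence is not exclusion.** The article condenses a longer protocol, where a covariate may be named. It remains that the article fixes both analyses in one section and gives the covariate to one only.
4. **An unadjusted comparison is legitimate.** This stands. It controls type I error, its standard error already reflects chance imbalance, and on the change reading baseline is subtracted. A reader might infer bias or an invalid primary test; nothing supports that. Nor would adjustment guarantee agreement between the primary and secondary results, since a sum and its components test different hypotheses.

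**Conclusion.** The point holds as a free improvement. As described, the gating test forgoes a covariate that is collected and used elsewhere for the same scales, and it is less precise than the adjusted version on either reading of the endpoint whenever 0 < r < 1. On change scores the benefit is modest at planned effects and more useful in the dilution scenario that the Discussion itself raises, where it adds about 8 percentage points at r = 0.5. The inconsistent wording is the part with the larger possible cost, but that cost arises only if raw week-52 values are tested and r is about 0.6 or more. The power figures rest on the assumed ρ of 0.7 and the assumed range of r; the direction of the precision gain does not.

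**What to change.** Define the primary AUSCAN endpoint once and use that definition in the abstract, hypothesis, endpoint table, sample size, statistical methods and discussion. Form the standardised pain-function sum per patient, state which standard deviations are used to standardise, and compare the arms in a linear model with baseline pain and baseline function as covariates. With the same standardising constants, this gives the same treatment effect whether the sum is built from changes or from week-52 scores. The secondary subscale ANCOVA already has its baseline covariate and needs no change.

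The cost is wording in the protocol and analysis plan, settled before unblinding. No new data, visits or patients are needed.

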### Participants and recruitment

Patients with hand OA according to the classification criteria of the American College of Rheumatology (ACR) with recent X-ray of the hands [22], dating from less than six months and showing radiological signs of digital erosive OA as defined by grades 2 or higher, per the Kellgren and Lawrence scale in one or more joints [23].

Participants must meet the inclusion and exclusion criteria in order to participate. These will be assessed at the screening visit. The key inclusion and exclusion criteria are listed in Table 1.

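### Screening AUSCAN scores are collected before randomization but have no stated use in the pain and function ANCOVAs; adding them would be a small, free gain in precision

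*Protocol article*

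**What the plan says.** Participants and recruitment says of the inclusion and exclusion criteria: "These will be assessed at the screening visit". Table 1 has two AUSCAN criteria: pain above 4 (criterion 5) and function of at least 26 (criterion 6). Every randomized patient therefore needs a screening AUSCAN. The visit schedule, printed under the Table 3 caption, agrees. It lists the AUSCAN among the enrollment investigations (30 days before baseline) and again among the baseline variables.

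Statistical methods tests the first primary hypothesis with a standardized sum of AUSCAN pain and function and names no covariate for that test. For pain, function and SF-36 as secondary outcomes it says: "Parametric ANCOVA with baseline status as co-variable will be applied to compare secondary outcomes". It does not say which visit or visits make up baseline status, and it does not mention the screening score.

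Sample size takes its effect sizes from change scores ("We considered differences in change scores in the AUSCAN scales pain and hand function") and claims "at least 80% power when comparing the two AUSCAN subscales pain and hand function separately".

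**The concern.** A self-reported score at one visit is a noisy measure of the patient's pre-treatment state. A second reading a few weeks earlier usually carries some extra prognostic information, and covariate adjustment can use it to reduce residual variance. That reading exists for every patient here, so the gain needs no visit, patient or data item beyond those planned. At stake are slightly narrower confidence intervals and slightly higher power in the separate pain and function comparisons. Function matters more, because its assumed effect size is the smaller of the two.

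**Working it through.** **Inputs from the protocol article.** Effect sizes and SDs: "we aim to detect an effect size (ES) of 0.4 for pain (SD: 4.3) and of 0.25 for function (SD: 7.3". There are 255 patients per arm, allocated "in a ratio of 1:1". The familywise error rate is 5%; sidedness is not stated, so two-sided is assumed.

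**Inputs assumed, because the documents give none.** q is the correlation of screening with baseline AUSCAN, 0.6 to 0.9 (central 0.75). ρ is the correlation of each of these with week 52, 0.4 to 0.6 (central 0.5). Variances are equal before selection. The entry threshold is taken as one SD below the screening mean.

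**Step 1: the plan's own figures, with no covariate.** Power ≈ Φ(ES·√(n/2) − 1.96).
- Function: 0.25 × √127.5 = 2.823; Φ(0.863) = 80.6% (80.4% with the t distribution).
- Pain: ES 0.4 gives 99.5%.
- Standardized sum: ES = (0.4 + 0.25)/√(2(1 + r)), where r is the pain–function correlation. At r = 1 this is 0.325 and power is 95.6%; at r = 0.5 it is 98.9%.

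The stated 80% and 95% both reproduce.

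**Step 2: residual variance without selection at entry.** With one pre-dose score it is 1 − ρ². With both it is 1 − 2ρ²/(1 + q).

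| ρ | q | one score | both scores | ratio |
|---|---|---|---|---|
| 0.4 | 0.9 | 0.840 | 0.832 | 0.990 |
| 0.5 | 0.75 | 0.750 | 0.714 | 0.952 |
| 0.6 | 0.6 | 0.640 | 0.550 | 0.859 |

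**Step 3: allow for selection on the screening score.** The entry thresholds cut off the lower end of the screening distribution, which weakens it as a predictor. Simulating the three scores (2 million draws) and keeping patients above the cut-off changes the three ratios to 0.991, 0.962 and 0.894. The saving is therefore about 1% to 11%, and about 4% at central values. At central values this equals 255/0.962 ≈ 265 per arm analysed with one score, or about 10 extra patients per arm.

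**Step 4: function power.** The answer depends on which SD the effect size of 0.25 refers to.
- If it refers to the residual SD of the one-baseline ANCOVA, the effect becomes 0.25/√ratio. Power moves from 80.4% to between 80.8% and 84.6%. At central values 0.25/√0.962 = 0.255, giving 82.0%, a gain of about 1.5 points.
- If it refers to the change-score SD, as Sample size suggests, one-baseline ANCOVA already improves on the stated figure. Without selection, its residual variance relative to the change-score variance is (1 + ρ)/2. At ρ = 0.5 this is 0.75, so the effect is 0.25/√0.75 = 0.289 and power is about 90%. In the simulation with selection, power with one baseline is about 87% to 92% over the assumed range. Adding screening gains 0.3 to 3 points, and about 1 point at central values (89.8% to 90.9%).

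Pain, at 99.5%, has almost nothing to gain in power; its interval would still narrow.

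**The case against.** The strongest case against is that nothing here is wrong. The article does not say that baseline status is one reading or that the screening score is excluded. It could mean an average, and its definition is ordinary SAP content. The SAP is not shown. That stands, and it is why this is only a suggestion.

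Three stronger readings are tempting, and the documents do not support them.
- **The confirmatory test loses precision.** The quoted sentence covers only the secondary ANCOVAs. No covariate is named for the standardized-sum test, so no loss can be read into it from this sentence.
- **The function comparison has almost no reserve.** The 80.4% is an unadjusted figure. If the effect size is on the change-score SD, the planned ANCOVA already has about 87% to 92% under the assumed correlations.
- **A larger saving is available by averaging the two readings and analysing change from that mean.** The Abstract and Discussion describe the endpoints as changes, but Statistical methods specifies ANCOVA for separate pain and function, not a raw change-score analysis.

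It can also be objected that the two readings may not reflect the same state. Standard therapy must be steady for two weeks before enrollment, whereas screening may be up to 30 days before baseline. The range above assumes that both readings predict week 52 equally well. If screening predicts less well, the gain shrinks. It vanishes when the screening correlation with week 52 equals q times the baseline correlation, for example 0.75 × 0.5 = 0.375. This limits the benefit, but a separate covariate that adds little simply receives little weight.

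The schedule was damaged in extraction, and its Day 0 column should not be counted as a third reading. That does not affect the point, because the eligibility rule alone establishes the screening score.

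**Conclusion.** The point holds as an optional gain in precision for the separate AUSCAN pain and function comparisons. A pre-randomization score that eligibility requires has no stated use in the analysis. Adding it would cut residual variance by about 1% to 11% (about 4% central), worth roughly 0.3 to 4 power points for function (about 1 to 1.5 central). These figures rest on correlations and an entry cut-off that the documents do not give, and on screening and baseline predicting week 52 equally well. The stated sample size and power stand without the change, and neither type I error nor bias is at issue.

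**What to change.** In Statistical methods, or in the SAP before unblinding:
- Define baseline status for AUSCAN as the last score before the first dose.
- In the ANCOVAs of AUSCAN pain and of AUSCAN function, enter the screening score of the same subscale as a second covariate beside it.
- If a covariate-adjusted version of the standardized-sum test is planned, include the screening scores there too.

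Both scores precede randomization, so the adjustment introduces no bias. The cost is one sentence and one degree of freedom per scale, out of 510 − 2 = 508 in the unadjusted two-group comparison. No new data are needed.
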